### Outcome measures

Outcome measures are collected at the entry visit and each applicable poststroke time point, according to the patient’s ability. Depending on functional ability, not all components may be feasible at early assessments. Participants who are not yet able to perform the exergame tasks will complete the feasible clinical assessments and PROMs only, and sensor-based exergame assessments will be added at later time points when they can be performed safely. For example, seated reaching may become feasible before standing reaching and gait initiation as motor ability improves. An overview of all outcome measures, including data sources, is provided in table 1.

**Table 1 T1:** Outcome measures, instruments and data sources

Outcome category	Outcome/variable	Data source
Patient characteristics		
	Sociodemographic profile (age, sex, occupation, ethnicity, education)	Medical record
	Stroke descriptors and relevant comorbidities (lesion side and site, type, aetiology, AF status/subtype)	Medical record
	Acute stroke severity	NIHSS
	Global cognition	MoCA
Sensor-based outcomes		
Exergame assessments	Postural control* (eg, postural sway)	IMUs; force plates
	Weight distribution*	Force plates
	Neuromuscular activity*	sEMG
	Movement coordination*	IMUs; Kinect; force plates
	Task accuracy (reach/step)	Kinect
	Upper-limb acceleration	IMUs
	Reaction and movement time	Kinect
Out-of-lab monitoring	Daily activity profile	Activ8 sensor
Clinical and patient-reported outcomes		
Clinical assessments	Lower-limb motor impairment	FM-LE (0–34); MI (0–100)
	Dynamic sitting balance	TIS (0–6)
	Standing balance	Mini-BEST (0–28) or BBS (0–56)
	Walking speed	10mWT (m/s)
	Ambulation category	FAC (0–5)
	Global disability	mRS (0–5)
PROMs	Anxiety and depression	HADS (0–21 subscores)
	Quality of life (health-related)	SF-36 (domain scores 0–100)

* Primary outcome domain. The four primary outcome domains are equally ranked, with no further hierarchy. All other outcome measures are secondary.

AF, atrial fibrillation; BBS, Berg Balance Scale; FAC, Functional Ambulation Categories; FM-LE, Fugl–Meyer Assessment-Lower Extremity; HADS, Hospital Anxiety and Depression Scale; IMUs, inertial measurement units; MI, Motricity Index; Mini-BESTest, Mini-Balance Evaluation Systems Test; MoCA, Montreal Cognitive Assessment; mRS, modified Rankin Scale; 10mWT, 10 m Walk Test; NIHSS, National Institutes of Health Stroke Scale; PROMs, patient-reported outcome measures; sEMG, surface electromyography; SF-36, 36 Item Short Form Health Survey; TIS, Trunk Impairment Scale.

#### Sociodemographic and clinical characteristics

At the entry visit, data are collected to describe the study population and support exploratory analyses. Sociodemographic and clinical information are extracted from medical records, including age, biological sex, occupation, ethnicity, educational level, lesion side and site, stroke type and aetiology, relevant comorbidities, and where documented, AF status and subtype and the National Institutes of Health Stroke Scale score from the acute hospital. Cognitive function at admission is screened using the Montreal Cognitive Assessment, a validated tool covering multiple cognitive domains.^50
51^

#### Sensor-based outcome measures

Sensor-based outcome measures are derived from the recordings obtained during seated reaching, standing reaching and gait initiation. Across the two levels of the game, these outcome measures capture anticipatory and reactive postural control, assessed both prior to and during the self-initiated functional tasks. Attention is given to both the timing and amplitude of postural responses and neuromuscular activity. Weight distribution and related asymmetry metrics will be used to quantify loading differences between the paretic and non-paretic sides. Movement coordination will be characterised by the relative timing between arm, trunk and pelvis motion during reaching and, during standing tasks, between postural weight shift and the reaching or stepping movement. Together, these outcomes provide quantitative markers of movement strategies that may enable examination of behavioural restitution and compensatory adaptations over time.^28
52^

Examples of modality-specific outcome measures include, among others, parameters derived from force plates such as centre-of-pressure trajectories, ground reaction forces and weight distribution. IMUs capture segmental accelerations and orientation-based estimates of postural sway, while sEMG signals provide muscle activation onset, amplitude and co-activation patterns. Kinect recordings capture segmental kinematics in the frontal plane, reaction and movement time and task accuracy. Together, this integrated setup enables the extraction of synchronised kinetic, kinematic and neuromuscular outcomes during each functional task. Out-of-lab monitoring is performed using a wearable activity sensor (Activ8), which enables continuous assessment of free-living movement behaviour outside the controlled laboratory environment. Daily activity, quantifying the time spent sitting, standing and walking, will be assessed during a 72-hour period.

#### Clinical and PROMs

The clinical test battery includes standardised instruments to assess lower extremity function and motor impairment, including balance, gait, strength, functional independence and psychosocial well-being. Lower limb motor performance is evaluated using the FMA–Lower Extremity and the Motricity Index. Both instruments demonstrate excellent reliability in stroke populations.^53–56^ Dynamic sitting balance is assessed with the dynamic subtest of the Trunk Impairment Scale, a validated and reliable tool recommended for stroke rehabilitation.^4
57^ Standing balance is evaluated using either the Mini-Balance Evaluation Systems Test and/or the BBS*,* depending on ambulatory capacity. Both scales have strong psychometric properties.^4
58
59^

Walking performance and independence are assessed using the 10 m Walk Test and the Functional Ambulation Category, which are reliable, valid and widely used in stroke rehabilitation.^60–63^ Global functional status is documented using the Modified Rankin Scale, widely used in clinical trials for its simplicity and reliability in measuring poststroke disability.^64^ Mental health and health-related quality of life are assessed with the Hospital Anxiety and Depression Scale and the 36-item Short Form Survey, both of which are validated instruments with good reliability in neurological populations.^65
66^

### Data analyses

#### Sample size

Assessments are expected to take place over a 36-month period, and the study aims to enrol 100 participants. This target was defined pragmatically based on the average admission flow at the rehabilitation site, where approximately seven patients per month are expected to be screened, of whom an average of three are expected to meet the eligibility criteria and be included. The planned sample is considered appropriate for the observational design of the study and its objective of describing longitudinal recovery trajectories across repeated assessments in a real-world rehabilitation cohort.

#### Statistical analysis

For the primary objective, longitudinal change in outcomes representing the four primary sensor-based domains (postural control, weight distribution, movement coordination and neuromuscular activity) will be analysed using linear mixed-effects models. Secondary longitudinal analyses will apply the same modelling framework to task-performance measures, daily activity, clinical outcomes and PROMs. Baseline characteristics will be summarised descriptively. Feasibility and data availability will be reported per assessment timepoint, documenting (1) the proportion of participants completing each assessment, (2) the number of valid trials per condition for sensor-based tasks and (3) reasons for missing data at each timepoint.

To investigate longitudinal change, each outcome will be modelled as a function of Time (categorical: baseline, week 5, week 8, week 12 and week 24). Models will include subject-specific random intercepts to account for baseline differences between individuals. Where supported by convergence and reliable variance estimation, random slopes for Time will be added to capture heterogeneity in individual recovery trajectories.^67
68^ Estimated marginal means will be used to describe group-level recovery trajectories, and post hoc contrasts will quantify differences across the full study period and between assessment intervals. Within each outcome domain, multiplicity will be controlled using Holm-Bonferroni correction.

Individual predicted trajectories will be visualised by combining individual intercept and slope estimates with the fixed effects. These individual trajectories will be plotted alongside group-level trajectories to illustrate both average trends and the distribution of recovery profiles across participants. Standard diagnostic checks will be performed; if assumptions are violated, transformations or alternative model specifications will be considered.

To examine associations between sensor-derived metrics of movement quality and clinical outcome measures, a multivariate mixed-effects modelling approach will be used. First, separate linear mixed-effects models will be fitted for each individual outcome, using the same model structure described above for the longitudinal analyses. These models provide subject-specific random intercepts and, when supported by convergence, random slopes for Time, representing each participant’s baseline level and rate of change.

Next, bivariate (joint) mixed-effects models will be constructed to quantify the association between selected pairs of outcomes, that is, one sensor-derived metric and one clinical measure. Pairings will be defined based on theoretical considerations and clinical relevance. These models estimate the covariance between the random effects of the two outcomes, from which we will estimate (1) the correlation between random intercepts, reflecting the association between participants’ baseline sensor-based movement quality and their baseline clinical performance and (2) the correlation between random slopes, reflecting whether improvements in sensor-derived outcomes correspond to improvements on clinical measures over time.

Correlations will be interpreted descriptively using conventional thresholds (eg, negligible, low, moderate, high, very high). Because this aim is exploratory, α=0.05 will be used without correction for multiple comparisons. Associations will be visualised using scatterplots of individual random effects and bivariate trajectory plots.

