### Assessment protocol

Each participant undergoes an entry visit (first study assessment) as soon as feasible after admission and informed consent. Follow-up assessments are scheduled within predefined poststroke windows at 5, 8, 12 and 24 weeks after stroke onset. As participants are eligible for inclusion within the first 8 weeks poststroke, they will complete between three and five assessments depending on their admission timing. Participants admitted later in the recovery trajectory (eg, around week 7–8 poststroke) will be scheduled at the first possible window and will subsequently be followed at the remaining scheduled windows (eg, weeks 8, 12 and 24) (figure 1).

All assessments are conducted by trained researchers, under standardised conditions in the hospital’s motion analysis lab (see further). Sessions are integrated into the rehabilitation schedule to minimise interference with therapy and last up to 120 min, including rest breaks as needed. When participants are discharged before a scheduled time point, outpatient follow-up is arranged whenever feasible.

The protocol consists of two components: (1) a series of structured, sensor-based recordings during functional activities obtained through an exergame and (2) a standardised set of clinical tests and PROMs, conducted without sensors. The clinical assessments and PROMs are completed whenever feasible, whereas the sensor-based exergame assessments are only performed when the participant is judged able to complete the respective task safely under supervision.

The sensor-based assessments are performed through an interactive game environment. The game interface (figure 1B) visualises an avatar, controlled by the participant’s non-paretic hand or a leg, who can move toward a target object. This game uses Kinect V2 markerless motion capture, placed in front of the participant, to track full-body movements in the frontal plane. Visual targets are presented on a screen to elicit controlled reaching or stepping movements. These tasks are designed to safely challenge postural control through controlled destabilisation and to elicit natural, functionally relevant movement responses.

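### If random slopes are dropped, the stated model falls back to equal correlation between all visits, so the full-period interval is probably too narrow and the early adjacent intervals too wide

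*Protocol article*

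**What the plan says.** The Statistical analysis section of the protocol article sets the longitudinal model in four steps.

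- Fixed part: "each outcome will be modelled as a function of Time (categorical: baseline, week 5, week 8, week 12 and week 24").
- Random part, always present: "Models will include subject-specific random intercepts to account for baseline differences between individuals".
- Conditional extension: "Where supported by convergence and reliable variance estimation, random slopes for Time will be added to capture heterogeneity in individual recovery trajectories".
- Use: "post hoc contrasts will quantify differences across the full study period and between assessment intervals", with Holm-Bonferroni correction within each outcome domain.

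The only general safeguard is: "Standard diagnostic checks will be performed; if assumptions are violated, transformations or alternative model specifications will be considered". No residual correlation structure and no robust standard error is named.

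On the design, the Assessment protocol section says "Follow-up assessments are scheduled within predefined poststroke windows at 5, 8, 12 and 24 weeks after stroke onset" and that participants "they will complete between three and five assessments depending on their admission timing". Under Sample size, "the study aims to enrol 100 participants", a target set pragmatically from admission flow.

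**The concern.** A random intercept with independent residuals is compound symmetry: one variance for every visit, and one correlation for every pair. Weeks 5 and 8 are then treated as no more alike than entry and week 24. The Introduction argues the opposite about recovery: patients differ widely in their course, and gains come early and then level off. People who change at different rates do not produce equal correlations over unevenly spaced visits.

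The rule for adding slopes does not protect against this. Failure to converge says little about whether slopes really vary, so real heterogeneity can be discarded for numerical reasons. The contrasts at stake serve the primary objective, and their standard errors feed the Holm-adjusted p-values.

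**Working it through.** **No figure to reproduce.** The article states no standard deviation, correlation, power or interval width. Every covariance below is an assumption.

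**Can categorical slopes be fitted?** The only Time variable defined is categorical with five levels. An intercept plus four Time effects is five random effects. Their unstructured covariance has 5 × 6 / 2 = 15 parameters, and the residual variance makes 16. Five visits with one value each give 5 variances + 10 covariances = 15 distinct entries. Sixteen parameters cannot be identified from 15 entries. On this reading the slopes must be dropped.

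**Size under linear random slopes.** Assume complete data and visits at weeks 3 (entry), 5, 8, 12 and 24. Let s² be the residual variance, b² the slope variance and d the gap in weeks.

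- True contrast variance per person: 2s² + b²d².
- Variance reported by the random-intercept model: 2(s² + b²S²), where S² is the sample variance of the visit times. Their mean is 10.4 and the squared deviations are 54.76 + 29.16 + 5.76 + 2.56 + 184.96 = 277.2, so S² = 277.2 / 4 = 69.3.
- Reliability R of individual entry-to-week-24 change (d = 21, d² = 441): b² × 441 / (2s² + b² × 441).

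With s² = 1 and R = 0.7, the true full-period variance is 2 / 0.3 = 6.67 and b² = 4.67 / 441 = 0.01058. The model variance is 2(1 + 0.01058 × 69.3) = 3.47 for every contrast.

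- Entry to 24: √(6.67 / 3.47) = 1.39, so a 95% interval covers 84%.
- Week 5 to 8 (d² = 9): √(2.095 / 3.467) = 0.78, so the interval is 1 / 0.777 = 1.29 times as wide as it should be.
- Week 12 to 24 (d² = 144): √(3.524 / 3.467) = 1.01, about right.

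| R | True/model SE, entry–24 | Coverage | True/model SE, 5–8 | True/model SE, 12–24 |
|---|---|---|---|---|
| 0.5 | 1.23 | 89% | 0.88 | 1.005 |
| 0.7 | 1.39 | 84% | 0.78 | 1.008 |
| 0.8 | 1.49 | 81% | 0.69 | 1.011 |

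**Other assumed structures, complete data.** Entries are now model SE / true SE, so below 1 is too narrow. Coverage is in brackets where it falls clearly below 95%. The linear-slope rows use intercept variance 0.7 and residual variance 0.3.

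| Assumed truth | Entry–24 | Entry–5 | 5–8 | 8–12 | 12–24 |
|---|---|---|---|---|---|
| Compound symmetry | 1.00 | 1.00 | 1.00 | 1.00 | 1.00 |
| AR(1) by visit order, 0.8 | 0.76 (86.6%) | 1.31 | 1.31 | 1.31 | 1.31 |
| Exponential decay, 0.95 per week | 0.74 (85.4%) | 1.93 | 1.59 | 1.40 | 0.89 (91.8%) |
| Linear slope SD 0.02 per week | 0.92 (92.8%) | 1.04 | 1.04 | 1.04 | 1.00 |
| Linear slope SD 0.06 per week | 0.71 (83.5%) | 1.34 | 1.32 | 1.29 | 0.99 |
| Decay on a plateauing recovery clock | 0.76 (86.3%) | 1.17 | 1.17 | 1.41 | 1.95 |
| Declining SD, exponential decay | 0.68 (81.9%) | 1.50 | 1.47 | 1.57 | 1.26 |

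**Unbalanced data.** REML random-intercept fits were simulated with n = 100 and 600 replicates. One third of participants had all five visits, one third lacked week 5, one third had only weeks 8, 12 and 24, and 20% missed week 24. Entry-to-24 coverage was 87.7% (exponential), 90.5% (linear slope, SD 0.04), 86.2% (plateauing clock) and 83.5% (AR(1)). Week 12 to 24 coverage was 91.5%, 93.0%, 99.7% and 98.0% in the same order. With true compound symmetry (400 replicates), entry-to-24 coverage was 94.8%.

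**The case against.** The strongest reply is that the plan is not a random-intercept plan. Slopes are to be added where supported, precisely to capture different recovery rates. The same section speaks of one slope per participant as a rate of change, which fits numeric time better than four categorical effects. A numeric slope is identifiable with three to five visits. In simulations with true linear slopes (n = 100, 60 replicates per setting), an intercept-plus-numeric-slope model reached a non-singular fit in 98–100% of runs, and full-period coverage was 92–100%. The article also does not say that sensor outcomes are reduced to one value per visit; at least five targets per side are recorded per task. This stands. A reader might infer that most outcomes will end up with compound symmetry, and the document does not support that.

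A reader might also infer that every adjacent-visit interval is too wide. It is not so: week 12 to 24 is about right under linear slopes, too narrow under calendar-time decay, and too wide where late visits resemble each other closely.

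It can further be said that covariance structure belongs in an analysis plan that is not shown. That would answer silence, but the article states a rule: intercept always, slopes if they fit. The promise to consider alternatives after diagnostics names no trigger, structure or order, so it leaves the choice until the data have been seen.

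**Conclusion.** The point holds in conditional form. For any outcome whose slopes are dropped, the stated model imposes equal variance and equal correlation on unevenly spaced visits. In every structure tried in which correlation falls with separation, the full-period interval was too narrow, covering about 81% to 93% instead of 95%, and the three early adjacent intervals were too wide, from 4% to nearly double with complete data. The week 12 to 24 interval has no settled direction. If the truth is compound symmetry, or if a numeric-time slope is fitted and describes the data, this error is absent or small.

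The sizes depend on assumed correlations, an assumed entry at week 3 and assumed missing-visit patterns; they are not predictions for this cohort. How often slopes will be dropped cannot be known from the article. The change is worth making because it concerns the primary contrasts.

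**What to change.** For the models behind the visit contrasts, specify an unstructured within-participant covariance over the five visits with Kenward-Roger degrees of freedom. State in advance one simpler structure for outcomes with sparse early data, for example a heterogeneous AR(1) or a correlation that decays with weeks since stroke. Require cluster-robust standard errors whenever only the random-intercept model fits. Keep random slopes for the individual-trajectory and bivariate analyses, and say that they are on numeric time.

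The cost is a sentence or two of text, and no data collection changes. Some intervals will widen, the full-period one above all. The unstructured model has 15 covariance parameters for at most about 100 participants. It may not fit for sensor outcomes that many cannot perform early or for which late entrants have no week 5 value, hence the stated fallback. Cluster-robust errors repair the standard errors only: where missing visits depend on earlier results, the estimates still lean on the working covariance.

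### Time is defined only as a five-level factor, yet the plan relies on one random slope per participant and one slope correlation per sensor–clinical pair

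*Protocol article*

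**What the plan says.** All of this is in the Statistical analysis section of the protocol article.

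- Fixed part: "each outcome will be modelled as a function of Time (categorical: baseline, week 5, week 8, week 12 and week 24". No numeric time variable is defined anywhere.
- Random intercepts are always included: "Models will include subject-specific random intercepts to account for baseline differences between individuals".
- Random slopes are conditional (the model must converge and its variances must be reliably estimated) and refer to the same Time: "random slopes for Time will be added to capture heterogeneity in individual recovery trajectories".
- The random effects are read as each participant's "baseline level and rate of change", and individual trajectories are to be drawn by "combining individual intercept and slope estimates with the fixed effects".
- The association analysis starts from separate models for each outcome "using the same model structure described above for the longitudinal analyses". It then fits joint models for pairs of one sensor metric and one clinical measure. The second target of those joint models is "the correlation between random slopes, reflecting whether improvements in sensor-derived outcomes correspond to improvements on clinical measures over time".

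The Introduction lists the association between sensor metrics and clinical measures among the secondary objectives. The Statistical analysis section calls that aim exploratory.

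**The concern.** A random slope is a single number per participant only if time enters the random part as a numeric variable. For a five-level factor, random slopes are four separate deviations from the reference visit, and none of them is a rate of change. The plan then asks for one correlation between slopes per pair, which this model does not contain.

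The estimation condition does not settle the matter. An over-parameterised fit can converge on a flat likelihood, so convergence alone would not expose the problem. If the slopes are dropped, the plan names no replacement for the slope correlation.

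At stake are the answer to whether sensor gains track clinical gains, and the individual trajectory plots. Under intercepts alone those plots become parallel lines.

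**Working it through.** There is no stated figure to reproduce: the section on sample size gives a pragmatic target of 100 with no power calculation. The check is whether the stated model determines the stated quantity.

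**Inputs from the protocol article.** Five Time levels (Statistical analysis). Three to five visits per participant (Assessment protocol). At least 5 targets per side for each sensor task (Assessment protocol). No repeat scoring of clinical scales within a visit is described. Each pair includes one clinical measure (Statistical analysis).

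**Assumptions.** Unstructured random-effect matrix G, free residual variance σ², one clinical score per visit, and all five visits observed (the best case). Participants with fewer visits inform only a subset of the same 15 moments.

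**Step 1: number of slopes.** A five-level factor gives 5 − 1 = 4 random deviations per outcome beyond the intercept. A pair of outcomes then has 4 × 4 = 16 cross-correlations among them, not one.

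**Step 2: one outcome, one score per visit.**
- Parameters: 5 × 6 / 2 = 15 in G, plus σ², which makes 16.
- Distinct marginal variances and covariances: 5 × 6 / 2 = 15.
- The numerical rank of the map from parameters to marginal covariance is 15.

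The reason is simple. The marginal covariance is V = ZGZ′ + σ²I, and with factor coding Z is an invertible 5 × 5 matrix. For any σ² below the smallest eigenvalue of V, G = Z⁻¹(V − σ²I)(Z⁻¹)′ is a valid matrix that gives the same V.

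In a simulated data set with N = 100, the log-likelihood was −595.4906 at each of the residual variances 0, 0.056, 0.111, 0.167 and 0.220. The variance of the week-24 deviation meanwhile fell from 1.51 to 1.07 (1.5117 − 2 × 0.2204 = 1.0709).

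**Step 3: the joint model.**

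| Values per visit (sensor, clinical) | Random part | Parameters | Rank |
|---|---|---|---|
| 1, 1 | factor | 55 + 2 = 57 | 55 |
| 5, 1 | factor | 57 | 56 |
| 1, 1 | one numeric slope | 10 + 2 = 12 | 12 |
| 1, 1, with residual covariance | one numeric slope | 13 | 13 |

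Here 55 = 10 × 11 / 2. Modelling sensor trials repairs the sensor side only: the one missing dimension in the second row is the clinical residual variance.

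**Step 4: what this does to a correlation (assumed values).** For both outcomes take intercept variance 1, SD of true change to week 24 of 0.7, residual variance 0.3, intercept and slope correlations 0.5, entry at week 3, and residuals independent between outcomes. The covariance of the two week-24 changes is 0.5 × 0.49 = 0.245. If σ² is the residual variance assigned to both outcomes, the implied correlation is 0.245 / (0.49 + 0.6 − 2σ²).
- σ² = 0: 0.245 / 1.09 = 0.22.
- σ² = 0.3: 0.245 / 0.49 = 0.50.

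If the sensor residual is pinned at 0.3 and only the clinical one is free, the lower end is 0.245 / √(0.49 × 1.09) = 0.34. The data cannot choose within either range, while the plan labels correlations by size.

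**Step 5: slopes dropped.** With random intercepts only, a participant's intercept is a constant shift over all visits. Its correlation between outcomes describes average level over follow-up. The plan describes it as an association at baseline.

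**The case against.** Several counter-arguments have weight.

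- **Sensor outcomes have repeated trials.** The article does not say that one value per visit is analysed. With 5 values per visit the single-outcome factor model is identified (16 parameters, rank 16). So it is not shown that random slopes fail for any primary outcome. This stands, but it does not help the pairs, each of which includes a clinical measure.
- **No covariance structure is stated.** A diagonal matrix has 6 parameters (intercept, four visit deviations, residual) and is identified from 15 moments. This stands for identification. It still yields four deviations and no single slope.
- **Slopes are conditional on more than convergence.** Reliable variance estimation is also required, and a flat likelihood would fail that if someone checked. This stands: the plan does not commit to an unidentified fit. But the clause leaves the slope correlation with no substitute.
- **A numeric slope was surely meant, and the analysis plan may define it.** The talk of a rate of change points that way. However, the article does not merely omit the coding: it defines Time as categorical and ties the slopes to that Time. Weeks, log weeks and visit number would also define different slopes, because the visits are unequally spaced.

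A reader might infer that the slope correlation does not exist as a quantity at all. The documents do not support that. Factor coding gives 16 correlations that are only partly determined under the assumptions above, and a numeric slope gives exactly one that is identified.

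**Conclusion.** Wrong as written, and should be fixed. The definition of Time and the planned single slope correlation contradict each other. The step from four deviations to 16 cross-correlations needs only the stated factor coding. Non-identification (16 parameters for 15 moments on the clinical side) rests on an unstructured matrix, a free residual variance and one clinical score per visit. The ranges 0.22 to 0.50 and 0.34 to 0.50 are illustrations under assumed values, not predictions for this study.

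A reader might also infer that the primary analysis fails. It does not. Categorical fixed Time with a random intercept, marginal means and contrasts can be fitted as described. Even an over-parameterised fit with one value per visit leaves the marginal covariance, and hence the visit means, unchanged. The damage is confined to the association analysis, which is secondary and exploratory, and to the individual trajectory plots. Exploratory status lowers the severity but does not make the quantity estimable.

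**What to change.** Amend the Statistical analysis section as follows.

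1. Keep Time categorical in the fixed part.
2. Define the random slope on one numeric scale, either actual weeks since stroke or its logarithm, chosen before analysis and centred at a stated time.
3. Describe the intercept correlation as the association at that centring time. If an association at baseline is meant, choose an early time, because a later one changes what this correlation measures.
4. Define the change association as the correlation of the two numeric-time slopes, with a 95% confidence interval.
5. State that it will be reported as not estimable if either slope variance cannot be estimated, and that the intercept correlation does not stand in for it.

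Each outcome then has 3 + 1 = 4 covariance parameters and each pair 12 or 13, all identified with one score per visit, and each pair has exactly one slope correlation.

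The cost is a few sentences and no new data. Recruitment was still under way at the reported status (56 included by July 2026), so the change can precede analysis. There is a small downside: one numeric slope simplifies individual courses in a recovery that the Introduction calls non-linear. The average course stays free, because fixed Time remains categorical.
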